### Economic assessment

Cost-effectiveness and cost-utility analysis will be carried out to evaluate the incremental cost per life-years adjusted for the quality (QALYs) of the interventions. The Fibromyalgia Impact Questionnaire will be used for cost-effectiveness analysis, and the EQ-5D-3L and SF-6D questionnaires will be used for cost-utility analysis. The costs measured in this study using resources by the participants will be: direct costs, which correspond to the costs of this participant to the public and private healthcare systems and the participant’s out-of-pocket expenses; and indirect costs through loss of productivity due to fibromyalgia. This assessment will be performed by information from a cost diary that the participants will keep at home. Three, six, nine, and 12 months after randomization, the assessor will collect these data by telephone. Thus, the costs of the interventions and the participants’ own expenses will be identified, measured, and validated. Table 2 shows the types of resources evaluated and the data sources from which the proposed information and evaluation methods will be taken. The number of work absences will be multiplied by the average salary rate to estimate the costs of paid work leave. Bus and subway fares or the price of fuel will be used to estimate transportation costs. Sensitivity analysis will test uncertainty in key parameters, such as the selection of cost weights and statistical variation in quality of life scores.

**Table 2 Tab2:** Assessment of the resource used

Resource type	Assessment tool	Assessment method	Sources consulted
Physical therapy sessions	Physical therapist report	Wage rates	Physical therapy board fee schedule
Medications, visits to doctors and/or health professionals of the public and private health systems, hospital stay, visits to emergency medical services	Questionnaires every three months	Published prices (costs for public and private health systems) and/or actual costs to participants	Pharmaceutical websites and medical services fee schedule
Visits to community or alternative services or alternative health professionals	Questionnaires every three months	Actual costs to participants	Health services fee schedule
Loss of productivity (assessed for hours of lost work)	Questionnaires every three months	Average wage in the state of Sao Paulo per hour for women and men	Brazilian Institute of Geography and Statistics website
Transport, public or private, for the use of each resource	Questionnaires every three months	Values of bus and subway tickets and fuel in the year in the state of Sao Paulo.	Sptrans, metrosp, national agency for oil, natural gas and biofuels websites

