### Assessment of clinical outcomes

Before baseline assessment, the participants will give consent and sign the Informed Consent Form. A blinded assessor will confirm the eligibility criteria and the diagnosis of fibromyalgia through the criteria of the American College of Rheumatology 2010 [2]. Next, demographic and anthropometric data will be collected, as well as information on the use of medications (type and quantity) for fibromyalgia and physical therapy or other previous treatment. Finally, the participants will be assessed for the primary and secondary outcomes. The assessments will be performed at baseline, eight weeks, six months, and 12 months after randomization, and in the last three assessments, the patients will be instructed not to provide information about their treatment to the blinded assessor. In the follow-ups assessments, patients will also be asked about the use of medication and physical activity or other treatment for fibromyalgia. The baseline and eight-week assessments will be face-to-face, and the six- and twelve-month assessments will be conducted over the phone to minimize loss to follow-up. In the eight-week assessment patients will also be asked about their satisfaction with the treatment. All of the scales and the questionnaire used in this study have already been translated and adapted to Brazilian Portuguese [29–41].

The primary outcome is the impact of fibromyalgia eight weeks after randomization. The secondary outcomes are: impact of fibromyalgia six and 12 months after randomization; pain intensity, kinesiophobia, sleep quality, health-related quality of life and specific disability eight weeks, six months, and 12 months after randomization; pain intensity at each session, before and after treatment; and functional capacity eight weeks after randomization (Table 1).

**Table 1 Tab1:** Description of the outcome measures

Measure	Construct	Description

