The cost-effectiveness analysis will be performed using the impact of fibromyalgia as outcome, and the cost-utility analysis using QALYs. Mean between-group cost differences will be calculated for total and disaggregated costs. Seemingly unrelated regression analyses will be performed in which effect and cost differences will be corrected for their baseline values if available, while also taking into account the possible correlation between effects and costs [54]. Incremental cost-effectiveness and cost-utility ratios will be calculated by dividing the corrected difference in total costs by the difference in effects. Uncertainty surrounding the cost differences and incremental cost-effectiveness and cost-utility ratios will be estimated using Bias Corrected and Accelerated bootstrapping techniques (5000 replications). The latter will be graphically presented in cost-effectiveness planes [55]. Cost-effectiveness acceptability curves will be estimated to indicate the intervention’ probability of being cost-effective compared with other at different values of willingness-to-pay [56]. The economic evaluation will be performed using STATA V.14.

In addition, a survival analysis will be performed to evaluate the number of sessions necessary for a 30% pain reduction compared to the initial pain, and this value was chosen because it is considered a minimal clinically significant difference in pain in patients with fibromyalgia [57]. This analysis will be performed using the Kaplan-Meier method [58] and the comparison between the groups by the Log-Rank test [59]. All analyses will follow the intention-to-treat principle. The significance level will be set at 5%. Table 3 shows the timeline of the study.

**Table 3 Tab3:** Timeline for the schedule of enrollment, interventions, and assessments

Outcomes	Enrollment	Before randomization	Intervention period (8 weeks)	8-week follow-up after randomization	6-month follow-up after randomization	12-month follow-up after randomization
Eligibility criteria	X					
Demographic data	X					
Informed consent	X					
Primary outcome						
Fibromyalgia impact		X		X		
Secondary outcomes						
Fibromyalgia impact					X	X
Pain intensity	X	X	X	X	X	X
Kinesiophobia		X		X	X	X
Specific disability		X		X	X	X
Health-related quality of life		X		X	X	X
Sleep quality		X		X	X	X
Functional capacity		X		X		
Interventions						
Aerobic exercise			X			
Pilates exercise			X			

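### Utility is not measured between the end of treatment and month 6, so a short-lived QALY gain could be overstated about twofold, although participants are already telephoned at month 3 for costs

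*Protocol article*

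**What the plan says.** **Costs.** Economic assessment in the protocol article has participants keep a cost diary, and for its contents states: "Three, six, nine, and 12 months after randomization, the assessor will collect these data by telephone". Table 2 agrees, with questionnaires every three months.

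**Utilities.** The same section says that "the EQ-5D-3L and SF-6D questionnaires will be used for cost-utility analysis". Assessment of clinical outcomes sets the schedule: "The assessments will be performed at baseline, eight weeks, six months, and 12 months after randomization". Its list of secondary outcomes gives the post-baseline times as "pain intensity, kinesiophobia, sleep quality, health-related quality of life and specific disability eight weeks, six months, and 12 months after randomization". Table 3 shows the same visits, with nothing at month 3 or month 9.

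**Mode.** Assessment of clinical outcomes adds that "the six- and twelve-month assessments will be conducted over the phone to minimize loss to follow-up", so these questionnaires are already to be given by telephone.

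**Analysis.** Statistical analysis says: "The cost-effectiveness analysis will be performed using the impact of fibromyalgia as outcome, and the cost-utility analysis using QALYs". The article gives no rule for joining utility values between visits. The sensitivity analyses that Economic assessment offers as examples are cost weights and statistical variation in quality of life scores. The path of utility between visits is not among them.

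**The concern.** Supervised exercise stops at 8 weeks, or at up to 10 weeks with make-up sessions (Interventions). The next utility reading is at month 6. How long any difference survives the end of supervision is thus filled in by the interpolation rule and not by data.

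The QALY difference is the denominator of the cost-utility ratio and also feeds the acceptability curve. The planned bootstrap resamples the observed values, so it cannot show error in a path that nobody observed. The Discussion offers the economic result to insurers and public health systems, and itself says that little is known about the longer-term effects of different exercise modalities in this condition.

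The gap arises from a fixed measurement schedule. An analysis plan can choose an interpolation rule, but it cannot supply readings that were not taken.

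**Working it through.** The article states no QALY or utility figure, so there is none to reproduce. The check measures how far the result depends on the unobserved interval.

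**Inputs from the article**
- Utility times: baseline, 8 weeks, 6 and 12 months (Assessment of clinical outcomes; Table 3).
- Telephone cost contacts: 3, 6, 9 and 12 months (Economic assessment).

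**Assumptions, not in the article**
- Area under straight lines between visits (trapezoid rule).
- Between-group utility difference of 0 at baseline and D at 8 weeks. Eight weeks is 8/52 = 0.154 year, or 1.85 months.

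**Scheduled grid, difference gone at months 6 and 12**

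Gain = ½ × 0.154 × D + ½ × (0.5 − 0.154) × D = 0.077D + 0.173D = 0.250D QALY (3.0D utility-months).

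The line from week 8 to month 6 implies a month-3 difference of 1 − (0.25 − 0.154)/(0.5 − 0.154) = 0.72D.

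**Other paths through the same scheduled readings (D at week 8, 0 at months 6 and 12)**

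| Actual path | Actual gain (QALY) | Scheduled grid ÷ actual |
|---|---|---|
| Lost straight after week 8 | ½ × 0.154D = 0.077D | 3.25 |
| Falls in a line to 0 at month 3 | ½ × 0.25D = 0.125D | 2.00 |
| Falls in a line to 0 at month 4 | ½ × 0.333D = 0.167D | 1.50 |
| Half left at month 3, then to 0 at month 6 | 0.077D + 0.072D + 0.0625D = 0.212D | 1.18 |
| All left at month 3, then to 0 at month 6 | 0.077D + 0.096D + 0.125D = 0.298D | 0.84 |
| Holds to month 5, then to 0 at month 6 | (0.92D + 3.15D + 0.5D)/12 = 0.381D | 0.66 |
| Holds until just before month 6 | 0.077D + 0.346D = 0.423D | 0.59 |

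The 2.00 does not change if the post-treatment reading falls at 10 weeks: both areas are triangles with height D, and their bases (0.5 and 0.25 year) do not depend on when the peak occurs.

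**Partial persistence, with an unseen zero at month 3 and month 9 on the line between months 6 and 12**

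| Left at month 6 / month 12 | Scheduled grid | Actual | Ratio |
|---|---|---|---|
| 0.25D / 0 | 0.356D | 0.219D | 1.63 |
| 0.5D / 0 | 0.462D | 0.313D | 1.48 |
| 0.5D / 0.5D | 0.587D | 0.438D | 1.34 |
| D / D | 0.923D | 0.750D | 1.23 |

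If D is kept from week 8 through month 12, both grids give 0.077D + 0.846D = 0.923D, a ratio of 1.00.

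**Effect on the cost-utility ratio.** The ratio is cost difference ÷ QALY difference. If the gain is overstated 2.0-fold, the reported ratio is 1/2.0 = 0.5 of the true one.

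**What a month-3 reading would do (utility-months)**
- Lost by month 3: estimate 1.5D against actual 1.5D. The error goes from 2.0-fold to none.
- Lost by month 4: the month-3 value is (4 − 3)/(4 − 1.85) = 0.46D. The estimate is 0.92D + 0.84D + 0.70D = 2.46D against 2.0D. The error goes from 1.5-fold to 1.23-fold.
- Holds to month 5: the estimate is 0.92D + 1.15D + 1.5D = 3.58D against 4.58D. The share captured goes from 66% to 78%.

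**The case against.** **No contradiction.** A reader might infer that the cost and utility calendars ought to coincide, and that their difference is an inconsistency. The article does not support that. Costs add up over a recall period, whereas utilities are values at a point in time, and the sections agree with each other on both schedules. Three post-baseline utilities in a year, one of them at the end of treatment, is a defensible choice. This objection stands, and the point is therefore a suggestion about design.

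**Interpolation is assumed.** The article gives no rule, and one may stand in a fuller document. That is fair, but any rule would have to fill the same unobserved interval.

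**Twofold is not a limit.** A reader might take it as the maximum or the expected error. It is neither. Loss straight after week 8 gives 3.25-fold, partial persistence with a zero at month 3 gives about 1.2 to 1.6, and a lasting effect gives 1.0. The Abstract expects the advantage to last. That expectation is what the trial is testing, so it does not settle the matter, but it does make twofold an unfavourable case.

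**Months 6 to 12.** A reader might count the whole period after week 8 (34.6% + 50% = about 85% of the year) as equally at risk. No error from months 6 to 12 has been calculated here, so the case for a month-9 reading is not quantified.

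**Small beside sampling error.** In the twofold case the absolute error is 0.125D, or 0.006 to 0.013 QALY for an assumed D of 0.05 to 0.10. Take 42 per arm (49 × 0.85), an assumed utility SD of 0.15 to 0.25 and a within-person correlation of 0.5. The visit weights are 0.077, 0.250, 0.423 and 0.250, and their squares sum to 0.310. The standard error of the QALY difference, before any baseline correction, is SD × √[(0.5 + 0.5 × 0.310) × 2/42] = SD × 0.177, or about 0.026 to 0.044. The interpolation error is smaller than that. This keeps the priority low, but the error is systematic and the reported intervals would not show it.

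**Conclusion.** The point holds as a low-priority, inexpensive improvement. The utility schedule leaves the interval from the end of treatment to month 6 unobserved, while a telephone contact at month 3 already falls inside it.

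Under straight-line interpolation, a gain present at 8 weeks and absent at 6 and 12 months would be overstated about twofold if it was lost by month 3, and the cost-utility ratio would be about half its true value. The size and direction depend on the path: smaller with partial persistence, none if the effect lasts, and an understatement (0.59 to 0.66 of the true gain) if it holds until month 5 or later and then goes. These figures rest on the interpolation rule and on assumed paths. None is a figure from the article.

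A reader might also infer that the cost-utility ratio is inflated along with the gain. It moves the other way, because the gain is its denominator.

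**What to change.** In Assessment of clinical outcomes, Economic assessment and Table 3:

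- Add the five EQ-5D-3L descriptive items to the existing 3-month cost call in both arms, asked before the cost questions. Add them to the 9-month call as well, so that the post-treatment utility readings follow the cost calls; the gain from that second reading is not quantified.
- Compute the EQ-5D QALY from baseline, 8 weeks, 3, 6, 9 and 12 months, and state the interpolation rule.
- Also report the EQ-5D QALY from baseline, 8 weeks, 6 and 12 months. It can then be compared with the SF-6D QALY on the same time points, and a difference between instruments is not confused with a difference between grids.
- Leave the role of SF-6D as Economic assessment has it. That section names both instruments for cost-utility and ranks neither.

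**Cost.** Five questions in each of two calls that every participant already receives, with no new visit or staff. The calls become slightly longer, a few more values may be missing, and an amendment is needed. Study settings provides for protocol changes to be registered before enrolment begins. The amendment should apply from that point, so that participants are not on mixed grids. The change reduces the interpolation error but does not always remove it.

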**Methods:**

In this randomized controlled trial with blinded assessor, 98 patients who meet the fibromyalgia classification criteria of the American College of Rheumatology 2010, aged between 20 and 75 years, and with pain intensity greater than or equal to 3 points in the Pain Numerical Rating Scale, will be randomly divided into Aerobic Group (aerobic exercises on treadmills or stationary bikes) and Pilates Group (modified Pilates exercises), and treated twice a week for eight weeks on the Center for Excellence in Clinical Research in Physical Therapy at Universidade Cidade de São Paulo, Brazil. The following outcomes will be evaluated by a blinded assessor at baseline, eight weeks, six months, and 12 months after randomization: impact of fibromyalgia assessed by the Fibromyalgia Impact Questionnaire, pain intensity by the Pain Numerical Rating Scale, kinesiophobia by the Tampa Scale of Kinesiophobia, specific disability by the Patient-Specific Functional Scale, functional capacity by the 6-min Walk Test, quality of sleep by the Pittsburgh Sleep Quality Index, and health-related quality of life by EQ-5D-3L and SF-6D questionnaires.

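### The assessor who should stay blinded also collects the cost diaries, and questions on activity, other treatment and satisfaction fall within the blinded assessments; this may unblind the 6- and 12-month telephone outcomes

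*Protocol article*

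**What the plan says.** The abstract's Methods paragraph assigns the outcomes to one role: "The following outcomes will be evaluated by a blinded assessor at baseline, eight weeks, six months, and 12 months after randomization". Under Assessment of clinical outcomes, baseline and week 8 are face to face, and months 6 and 12 are by telephone. The same section sets the safeguard: "in the last three assessments, the patients will be instructed not to provide information about their treatment to the blinded assessor".

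It then adds questions to those same contacts. "In the follow-ups assessments, patients will also be asked about the use of medication and physical activity or other treatment for fibromyalgia". And: "In the eight-week assessment patients will also be asked about their satisfaction with the treatment". Neither sentence says who asks, or at what point in the visit or call.

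Under Economic assessment, resource use is recorded in a diary kept at home, and: "Three, six, nine, and 12 months after randomization, the assessor will collect these data by telephone". Table 2 lists what is gathered every three months: medications, visits to doctors and other professionals, hospital and emergency care, alternative services, lost work, and "Transport, public or private, for the use of each resource". The trial's own physical therapy sessions are costed from the therapist's report. The Economic assessment text nevertheless says that this process identifies the costs of the interventions as well as participants' own spending.

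**The concern.** Participants and therapists know the allocation, as the Discussion acknowledges. At the point of data collection the assessor is the only blinded party, and the Discussion counts assessor blinding among the measures taken against bias.

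The safeguard is that patients keep quiet about their treatment. The tasks given to the same contacts work against it, because they ask what exercise or treatment the patient now has, how satisfied the patient was, and what services the patient has used. A participant who has carried on with Pilates, or with treadmill or bicycle training, could answer truthfully in a way that points to an arm.

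The 6- and 12-month questionnaires are administered by telephone, so an interviewer who has guessed the arm could influence how items are put or clarified. The abstract states that Pilates is expected to do better and to keep its advantage in the medium to long term, so any such influence could have a direction. The FIQ, EQ-5D-3L and SF-6D collected in this way also feed the cost-effectiveness and cost-utility analyses, which belong to the trial's stated aim.

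**Working it through.** No figure in the protocol bears on this point, so the check sets the schedule of contacts beside the tasks at each one. Sources are Assessment of clinical outcomes, Economic assessment with Table 2, and Table 3.

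| Contact after randomization | Clinical outcomes | Activity and other-treatment questions | Satisfaction | Cost diary | Non-disclosure instruction |
|---|---|---|---|---|---|
| 8 weeks, in person | Yes: primary FIQ, walk test, others | Yes | Yes | No | Yes |
| 3 months, telephone | No | No | No | Yes | Not stated |
| 6 months, telephone | Yes, no walk test | Yes | No | Yes | Yes |
| 9 months, telephone | No | No | No | Yes | Not stated |
| 12 months, telephone | Yes, no walk test | Yes | No | Yes | Yes |

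1. **Who makes the cost calls.** The text says the assessor, without the word blinded. No second assessor is described, so the natural reading is the same person.

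2. **Who asks the other questions.** The sentences are passive. That the blinded assessor asks them is an inference from their place within the assessments that person conducts.

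3. **Reach of the instruction.** It covers three assessments: 8 weeks, 6 months and 12 months. Of the four cost calls, two (3 and 9 months) fall outside it as written.

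4. **Order in time.** The first cost call, at 3 months, comes after the 8-week assessment. No cost call can therefore influence the primary outcome or the post-baseline walk test. One call (3 months) precedes the 6-month outcomes, and three (3, 6 and 9 months) precede the 12-month outcomes. The 6- and 12-month cost items also fall due with the outcomes at those times, in an order that is not given.

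5. **What the 3-month diary spans.** Treatment lasts 8 weeks and can be extended to 10 for make-up sessions (Interventions). Either length ends before 3 months, so the first diary covers the whole intervention period.

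6. **What could point to an arm.** Satisfaction alone names no arm. Session number and length (16 of 60 minutes) and the treatment centre are the same in both arms, so travel to trial sessions does not separate them. Answers about current exercise or about services used could do so. At week 8, participants have been asked not to seek other exercise-based or non-drug treatment (Eligibility criteria). An activity question may then draw little, or it may draw a description of the trial exercise itself. The text does not settle which.

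**The case against.** The strongest reply is that this is a narrow risk presented in a condensed article. The order of questions and the person asking ancillary items usually belong in the full protocol or an operating manual. Most diary items do not differ by arm, trial sessions are costed from therapist reports, and current exercise is an imperfect clue because participants in either arm may take up any activity after week 8. Participants are unblinded and every outcome except the walk test is self-reported, so an interviewer reading fixed questionnaires probably adds little to the bias already acknowledged. The walk test has scripted encouragement.

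Much of this stands, and it limits the point. Silence about question order would not be a finding by itself. The article is not silent on the cost calls, however: it gives them to the assessor, and it puts activity and treatment questions into contacts where disclosure is meant to be avoided. That is a stated arrangement that works against a stated safeguard.

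A reader might infer three stronger things that the documents do not support:

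- **That these tasks reveal allocation.** The text supports only that they may.
- **That the primary outcome is compromised by the cost calls.** The calendar rules this out.
- **That assessor blinding is the only blinding in the trial.** Under Statistical analysis the statistician is also blind to group, although that does not protect data collection.

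**Conclusion.** The point holds as a risk of unblinding at the 6- and 12-month telephone assessments, and it is worth correcting because correction is cheap. For the week-8 outcomes the risk is confined to the activity and satisfaction questions, and only if they are asked before the FIQ and walk test.

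The exposure can be counted (one cost call before the 6-month outcomes, three before the 12-month outcomes, two of four calls outside the instruction), but its effect cannot. The documents contain nothing from which to estimate interviewer bias, and expressing a point of FIQ as a share of the 8-point target would not measure it.

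The conclusion assumes that the assessor named under Economic assessment is the blinded outcome assessor and, for the activity and satisfaction items, that this person asks them. If the full protocol names someone else for these tasks, the concern falls away for those items.

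**What to change.** 1. At each follow-up, take all clinical outcomes first. Ask about activity, other treatment and satisfaction only afterwards.
2. Give the cost calls to an existing team member who does not assess outcomes, for example the student who does the telephone screening. At minimum, move the 3- and 9-month calls and ask the 6- and 12-month cost items after the outcomes.
3. Extend the non-disclosure instruction to every contact with the assessor.

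Ordering within a contact protects that contact's outcomes but not the next one's: what the assessor hears at the end of week 8 or month 6 is still known later. Moving all four cost calls is therefore better than the minimum option, and the same colleague could ask the activity items if the team wishes to close that gap too. A sealed, self-completed satisfaction sheet and a record of the assessor's guess of allocation are optional.

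The cost is reordered forms, calls reassigned within the present team and minor rescheduling. No extra participants or visits are needed.
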